#### Safety

The proportion of various procedural complications will be compared descriptively using chi-square tests to determine relative safety of CTA to ICA. Patient morbidity/health-related QOL associated with CTA and/or ICA will be compared using Student-t tests for the overall scores and utility.

The accuracy (operating characteristics) of CTA in the identification of high-risk coronary anatomy and obstructive CAD (per-patient/vessel/segment analysis) will be assessed in the cohort of patients undergoing both CTA and ICA. A receiver operating characteristic (ROC) curve analysis will be conducted for the vessel disease number, and the weighted kappa with 95% CI will be calculated to assess the agreement between CTA and ICA for the allocation of patients into the groups: 0-, 1-, 2- or 3-vessel disease; high-risk CAD; and non-high risk CAD. ROC analysis will also be performed on a per-patient, per-vessel and per-segment basis. In the patients who undergo both CTA and ICA, the accuracy of CTA to predict subsequent early revascularization will be assessed as follows: the point estimates with 95% CI for the sensitivity (S_e_), specificity (S_p_), positive predictive value (PPV), and negative predictive value (NPV) of CTA in identifying a patient for revascularization (medical therapy (no obstructive CAD) versus revascularization (PCI (non-high risk CAD) versus CABG (high-risk CAD)) using ICA as the gold standard will be calculated. They will be adjusted for referral bias using the Diamond method [18].

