### Hypotheses

The primary hypothesis is that, compared to ICA, a diagnostic strategy algorithm using CTA for HF patients will result in a reduction in downstream resource utilization leading to a reduction in average costs per patient.

The first of two secondary hypotheses states that compared to ICA (standard of care), a CTA strategy will achieve: a) similar composite clinical events (CCE) (cardiac death, myocardial infarction (MI), resuscitated cardiac arrest and cardiac re-hospitalization (worsening heart failure, acute coronary syndrome arrhythmia), QoL, and MACE (cardiac death, non-fatal MI); b) a lower rate of procedure related complications (death, MI, stroke, vascular complications, severe allergic reactions; contrast nephropathy); and c) a lower rate of normal ICA. The second of the two secondary hypotheses states that using patient-based analysis and vessel-based analysis, CTA has very good agreement with ICA among patients with HF in the CTA arm who proceed to ICA.

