## Methods/Design

### Design

CTA-HF is a multicenter, multinational, randomized controlled trial that is currently recruiting 250 patients from 15 sites across Canada and Finland (see Additional file 1) over 4 years, randomized to CTA versus ICA (n = 125 per group) as the first test to define coronary anatomy in patients with heart failure. This research study has approval from each participating center’s institutional research ethics board.

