### Outcome measures

The primary outcome (average health care costs per patient) will be determined through regression methods detailed below.

All secondary outcome measures will be determined: (CCE (cardiac death, myocardial infarction, resuscitated cardiac arrest and cardiac re-hospitalization (worsening heart failure, acute coronary syndrome arrhythmia), QoL, procedural complications (all-cause death, myocardial infarction, stroke, vascular complications, severe allergic reactions; contrast nephropathy), and rate of normal ICA.

CTA accuracy: To address the 2^nd^ secondary hypothesis, regarding CTA accuracy, the accuracy in the cohort of patients randomized to CTA and undergoing subsequent ICA (sensitivity, specificity, predictive values and likelihood ratios) will be determined and reported with 95% confidence intervals (CI). It is estimated that 50/125 of the patients randomized to CTA will have subsequent ICA, which will enable the comparison of CTA accuracy to ICA.

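### CTA sensitivity, specificity, likelihood ratios and ROC rest on the patients referred on to ICA, and the referral-bias adjustment is worded to cover only the revascularization estimates

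*Protocol article*

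**What the plan says.** Three places in the protocol article define the accuracy analysis.

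- **Outcome measures.** The second secondary hypothesis is addressed through "the accuracy in the cohort of patients randomized to CTA and undergoing subsequent ICA (sensitivity, specificity, predictive values and likelihood ratios"), each with a 95% CI. The section adds: "It is estimated that 50/125 of the patients randomized to CTA will have subsequent ICA". It mentions no adjustment.
- **Safety (under Secondary analysis).** The operating characteristics of CTA for high-risk anatomy and obstructive CAD "will be assessed in the cohort of patients undergoing both CTA and ICA". ROC analyses and a weighted kappa follow, again with no adjustment. The paragraph then turns to sensitivity, specificity, PPV and NPV "of CTA in identifying a patient for revascularization", and the next sentence reads: "They will be adjusted for referral bias using the Diamond method".
- **Hypotheses.** The agreement claim is that "CTA has very good agreement with ICA among patients with HF in the CTA arm who proceed to ICA".

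Three further statements bear on who is referred and on whom the results are meant to describe. The Invasive coronary angiography section sends the results of either test to the referring physician. The Hypotheses section expects fewer normal ICAs under the CTA strategy. The Discussion says that the trial will establish the diagnostic accuracy of CTA in undifferentiated heart failure, without restricting this to referred patients.

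**The concern.** ICA is the reference standard here, but CTA-arm patients undergo it only if someone decides to send them on after seeing the CTA result. If CTA-positive patients are sent more often than CTA-negative ones, the verified sample is short of both true negatives and false negatives. Sensitivity is then pushed up and specificity down, and the positive likelihood ratio, Se/(1 − Sp), falls with specificity. This is partial verification bias, which the plan itself calls referral bias.

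The plan recognizes the problem and names a remedy, but attaches it to one set of estimates. The sensitivity, specificity, likelihood ratios and ROC for obstructive and high-risk CAD come from the same selected patients and carry no stated adjustment. At stake are the accuracy figures for the second secondary hypothesis and the accuracy goal in the Discussion. CTA could appear almost perfectly sensitive and poorly specific through selection alone.

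**Working it through.** **The plan's own figure.** 50/125 = 0.40, so 40% of the CTA arm is expected to have the reference test. The arm size of 125 is confirmed in Design: "randomized to CTA versus ICA (n = 125 per group) as the first test to define coronary anatomy".

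**Assumed inputs (not in the article).** True Se 0.95, true Sp 0.85, prevalence of obstructive CAD 30%. The fraction r₊ of CTA-positive patients who are referred is varied. The fraction r₋ of CTA-negative patients is then set so that 50 are verified in total.

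**Expected table for all 125 patients.** Diseased 37.5, non-diseased 87.5.

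- TP = 37.5 × 0.95 = 35.625; FN = 1.875
- FP = 87.5 × 0.15 = 13.125; TN = 74.375
- CTA-positive = 48.75; CTA-negative = 76.25

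**Formulas.**

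- r₋ = (50 − 48.75 r₊)/76.25
- apparent Se = TP·r₊/(TP·r₊ + FN·r₋)
- apparent Sp = TN·r₋/(TN·r₋ + FP·r₊)
- LR+ = Se/(1 − Sp)

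**Example, r₊ = 0.80.** Verified positives 39, verified negatives 11, r₋ = 11/76.25 = 0.144. Se = 28.5/(28.5 + 0.27) = 0.991. Sp = 10.73/(10.73 + 10.5) = 0.505. LR+ = 0.991/0.495 = 2.0.

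| CTA-positives referred | CTA-negatives referred | Apparent Se | Apparent Sp | Apparent LR+ |
|---|---|---|---|---|
| 40% | 40.0% | 0.950 | 0.850 | 6.3 |
| 60% | 27.2% | 0.977 | 0.720 | 3.5 |
| 80% | 14.4% | 0.991 | 0.505 | 2.0 |
| 90% | 8.0% | 0.995 | 0.336 | 1.5 |

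The first row is referral unrelated to CTA, and it shows no bias.

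**Other assumptions.** With 80% of CTA-positives referred and the same true Se and Sp, apparent Sp is 0.61 at prevalence 20% and 0.24 at prevalence 40%. The check was repeated with true Se/Sp of 0.95/0.85, 0.90/0.80 and 0.95/0.65, prevalence 20% to 40%, and at least 60% of CTA-positives referred. Across these cases apparent Sp falls by about 0.11 to 0.77 and apparent Se rises by about 0.02 to 0.10.

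**Effect of the adjustment.** When referral depends only on the CTA result, PPV and NPV in the verified patients are undistorted: PPV = 35.625/48.75 = 0.731 and NPV = 74.375/76.25 = 0.975 in every row. Re-weighting them by the CTA totals in all 125 patients gives Se = 35.625/(35.625 + 1.875) = 0.95 and Sp = 74.375/(74.375 + 13.125) = 0.85, the assumed values.

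**Stability of the adjusted sensitivity.** In the 90% row about 6 CTA-negatives are verified (76.25 × 0.080 = 6.1). If none has CAD, adjusted Se is 100%. If one has, the imputed FN count is 76.25/6 = 12.7 and adjusted Se is 35.625/(35.625 + 12.7) = 0.74. The chance of at least one is 1 − 0.975⁶, about 14%.

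**The case against.** The strongest reply is that the plan already recognizes referral bias and names a method, and that a pronoun in a condensed article is thin evidence that the other estimates go uncorrected. The adjustment sentence does close the accuracy paragraph. Its natural antecedent, however, is the point estimates in the sentence before it, and Outcome measures promises sensitivity, specificity and likelihood ratios with no adjustment. Even if the wider meaning was intended, the text needs a sentence to say so.

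A reader might go further in four ways that the article does not support.

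- **Severe bias is certain.** No referral rule or referral rate by CTA result is given, so the bias can be anything from nil to very large. The stated aims make dependence on CTA likely, but they do not fix its strength.
- **Kappa is biased too.** The Hypotheses section defines agreement among CTA-arm patients who proceed to ICA. Kappa in that cohort estimates exactly that, and re-weighting it would change the hypothesis.
- **Adjusting PPV and NPV is a mistake.** If referral depends only on CTA, the adjustment leaves them unchanged. If it depends on other factors, they may need it.
- **Clustering of segments within patients is ignored.** The article gives no interval method for vessel or segment results. Silence is not a naive plan, and this detail is commonly left to an analysis plan.

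Two cautions about the remedy stand. Adjusted sensitivity can be unstable when few CTA-negatives undergo ICA, as shown above. CTA results also cannot be assumed for the whole arm, because Data analysis provides for patients who do not receive the allocated test.

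**Conclusion.** The point holds as one of scope. As written, the referral-bias adjustment covers the revascularization estimates but not the sensitivity, specificity, likelihood ratios and ROC for obstructive and high-risk CAD, which come from the same selected patients (about 40% of the CTA arm). Those estimates are likely to overstate sensitivity and understate specificity and LR+ for undifferentiated heart failure.

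With the assumed Se 95%, Sp 85% and prevalence 30%, referral of 60% to 90% of CTA-positives gives apparent Sp of about 0.72 to 0.34, Se of 0.98 to 0.995, and LR+ of 3.5 to 1.5 against a true 6.3. These figures illustrate and do not predict. The 2×2 model has no category for inconclusive scans and assumes that referral depends only on the CTA result.

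This should be corrected, but it concerns a secondary hypothesis. The primary cost comparison is unaffected.

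**What to change.** 1. State in Outcome measures and in Safety that the referral-bias adjustment (Diamond or Begg–Greenes) also applies to the per-patient sensitivity, specificity, likelihood ratios and ROC for obstructive and high-risk CAD, using the CTA results of all CTA-arm patients who were scanned.
2. Weight within each CTA grade, with inconclusive scans as their own category. State the assumption that referral depends only on what enters the adjustment.
3. Give bootstrap CIs, resampling all scanned patients and repeating the adjustment each time. Name a fallback interval for sensitivity in case no verified CTA-negative patient has disease, because every resample would then return 100%.
4. Report the unadjusted values alongside, labelled 'verified patients only', with the numbers of CTA-positive and CTA-negative patients who had ICA.
5. Leave kappa in the referred cohort, as the Hypotheses section defines it.

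If the sponsor prefers not to extend the adjustment, the alternative is to limit the accuracy statement in the Discussion to referred patients.

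The cost is wording and analysis code, with no new data collection. The downside is wider intervals and an adjusted sensitivity that may be unstable if few CTA-negative patients undergo ICA.

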#### Computed tomographic coronary angiography

Non-contrast enhanced prospective ECG-triggered image acquisition will be acquired and the Agatston score will be calculated [15]. Standard procedures will be applied for contrast infusion, timing and image acquisition. As per local clinical practice, prospective ECG-triggered or retrospective ECG-gated data sets will be acquired using bi- or tri-phasic contrast protocols. Vendor-specific radiation dose-reducing techniques such as prospective ECG-triggered image acquisition will be encouraged. A 4-point grading score [normal, mild (<50%), moderate (50 to 69%), severe (≥70%)] will be used for the evaluation of coronary stenosis using a 17-segment model. Similar to ICA, obstructive CAD is defined as coronary diameter stenosis ≥50% (Additional file 2).

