#### Invasive coronary angiography

ICA will be performed according to standard clinical protocols, with selective coronary injection and images acquired from multiple oblique views (Additional file 2).

Patients with obstructive CAD will be categorized as having high risk CAD (defined as having a left main stenosis (≥50%), or three-vessel disease (VD) (≥70%) or two-VD (≥70%) involving the proximal left anterior descending artery) or non-high risk CAD [9].

Following either CTA or ICA, information on the results will be disseminated to the referring physician as part of their standard clinical care.

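### The analysis described as CTA predicting early revascularisation is scored against ICA anatomy, so it measures obstructive CAD again and not revascularisation

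*Protocol article*

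**What the plan says.** The accuracy paragraph under Safety in the Protocol article contains two analyses that matter here, both in patients who have had CTA and ICA.

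- The first examines how well CTA detects obstructive CAD and high-risk anatomy, by patient, by vessel and by segment.
- The second is introduced with the words "the accuracy of CTA to predict subsequent early revascularization will be assessed as follows". It yields sensitivity, specificity, PPV and NPV with 95% confidence intervals, for the contrast "medical therapy (no obstructive CAD) versus revascularization (PCI (non-high risk CAD) versus CABG (high-risk CAD)) using ICA as the gold standard". The resulting estimates are then to be adjusted for referral bias by the Diamond method.

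The categories are defined under Interventions. The CTA section states: "Similar to ICA, obstructive CAD is defined as coronary diameter stenosis ≥50" per cent, so one threshold serves both tests. The ICA section adds the split: "Patients with obstructive CAD will be categorized as having high risk CAD" or non-high risk CAD, depending on left main, three-vessel or two-vessel involvement.

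**The concern.** The stated target is something that happens to the patient after imaging. The stated reference is what the ICA shows. They coincide only if every patient with obstructive CAD on ICA, and no other patient, is revascularised. The Background does not treat the two as the same: it links the possible benefit of revascularisation to viable myocardium as well as to ischaemic disease.

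Followed as written, the trial would publish a predictive value for revascularisation in which no revascularisation was counted. A patient with obstructive CAD on ICA who has no procedure would enter the table as revascularised. Under the article's grading and risk definitions, that includes a patient whose only lesion is a 50 to 69% stenosis outside the left main. A reader would take the PPV as the chance that a positive CTA leads to a procedure, when it is the chance that ICA confirms a stenosis.

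**Working it through.** The article gives no sample size, power or expected value for this analysis, so there is no stated figure to reproduce. The only related number is the expected cohort: 50 of 125 CTA patients going on to ICA, or 40% (Outcome measures).

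**Step 1: is the table the same as the obstructive-CAD table?** Set the article's categories side by side.

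| ICA finding | Label in the revascularisation analysis | Obstructive CAD |
|---|---|---|
| No obstructive CAD | Medical therapy | No |
| Obstructive, non-high risk | Revascularisation (PCI) | Yes |
| Obstructive, high risk | Revascularisation (CABG) | Yes |

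High risk and non-high risk together make up all obstructive CAD. The binary split is therefore obstructive CAD yes or no in every row. With the same threshold and mapping applied to CTA, the unadjusted sensitivity, specificity, PPV and NPV are those of the per-patient obstructive-CAD analysis. This step needs no assumed number. The PCI versus CABG split likewise follows the high-risk anatomy that the paragraph already examines through operating characteristics and weighted kappa.

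**Step 2: what would change with procedures performed as the reference?** Let TP, FN, FP and TN be cohort proportions against ICA anatomy, and r the share of patients with obstructive CAD who are revascularised early. Assume that nobody without obstructive CAD is revascularised, and that within obstructive CAD the decision does not depend on the CTA result. Then:

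- PPV for revascularisation = r × TP / (TP + FP) = r × anatomical PPV
- Specificity for revascularisation = [TN + (1 − r) FN] / [TN + FP + (1 − r)(TP + FN)]
- Sensitivity is unchanged

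**Step 3: illustration.** The article gives neither r, nor the prevalence of obstructive CAD, nor CTA accuracy. Every input below is assumed.

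With anatomical PPV 85%: r = 40% gives 0.40 × 0.85 = 34%, and r = 80% gives 0.80 × 0.85 = 68%.

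With prevalence 40%, sensitivity 95% and specificity 85% against anatomy: TP = 0.40 × 0.95 = 0.38, FN = 0.02, FP = 0.60 × 0.15 = 0.09, TN = 0.51.

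| r | Specificity | PPV |
|---|---|---|
| 100% | 85.0% | 80.9% |
| 75% | 73.6% | 60.6% |
| 50% | 65.0% | 40.4% |
| 30% | 59.5% | 24.3% |

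For r = 50%: PPV = 0.19 / (0.19 + 0.28) = 40.4%, and specificity = (0.51 + 0.01) / (0.51 + 0.09 + 0.20) = 0.52 / 0.80 = 65.0%.

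At prevalence 60% with the same accuracy, r = 50% gives specificity 50.7% and PPV 45.2%, against 85.0% and 90.5% when r = 100%.

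**Step 4: how firm is the direction?** The fall in PPV needs only that some patients positive on both tests go without a procedure and that nobody without obstructive CAD is revascularised. The fall in specificity also leans on the independence assumption: if the patients left without a procedure were mainly CTA-negative, it could shrink or reverse.

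**The case against.** The best defence is that the article also speaks of identifying a patient for revascularisation, which can mean candidacy on anatomical grounds and not treatment received. On that reading a patient with obstructive CAD who is managed medically is not misclassified. ICA as reference would also suit the article's only accuracy hypothesis, very good agreement with ICA, and revascularisation is not a listed outcome. It is also possible that ICA as gold standard was meant as the decision taken after ICA. None of this removes the mismatch. The sentence opens by naming a subsequent event, and its brackets assign treatment from anatomy alone. If candidacy was meant, the prediction wording is what has to change.

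Three further points on that side stand and limit the finding:

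- **Three classes.** A reader might infer that one set of sensitivity, specificity and predictive values cannot exist for medical therapy, PCI and CABG. The brackets are nested, however: the top-level contrast is medical therapy against revascularisation, which is binary. One set does exist.
- **Identical results.** A reader might infer that the reported figures must equal the obstructive-CAD figures. That holds only before adjustment. The Diamond correction is most naturally read as applying to this analysis and is not stated for the other, so the published estimates may differ.
- **Procedures already recorded.** A reader might infer that PCI and CABG are already in the costing data. The resource list names hospitalisations and further testing, but not these procedures. Their capture is likely through hospitalisations but is not documented.

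Performed procedures are not a clean reference either. CTA results go to the referring physician, so the index test can influence the outcome it is scored against. The length of the early window is ordinary analysis-plan detail, and its absence from an article is not counted against it.

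**Conclusion.** The point holds as a mismatch between stated target and stated reference. As written, the analysis repeats, before the Diamond adjustment, the per-patient obstructive-CAD classification under a treatment-prediction label, and it cannot support a statement about predicting revascularisation. That conclusion rests on the article's own definitions alone.

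The size of the overstatement is not known. The 34% to 68% range, and the specificity and PPV table, rest wholly on assumed inputs and on the two assumptions in Step 2. They show direction and possible scale, and a reader should not take them as estimates for this trial.

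The consequence is contained: one secondary accuracy analysis in about 50 patients. The primary cost comparison, the clinical event analyses and the complication comparison are unaffected. It should still be corrected, because it changes what the trial may claim about CTA and the correction is inexpensive.

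**What to change.** Make target and reference agree in one of two ways.

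1. **Keep the prediction question.** Score CTA as a binary result (obstructive or not) against PCI or CABG actually performed within an early window fixed in advance. First confirm that the hospitalisation data capture these procedures with dates. Describe the result as predictive value only, because CTA results reach the referring physician.
2. **Keep ICA anatomy as the reference.** Drop the revascularisation-prediction label and report the result as agreement on anatomical category, alongside the weighted kappa already planned.

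The second option costs only a change of wording. The first costs a wording change and a check of the data forms, plus a small addition to data collection if the procedures prove not to be captured. Either way the change concerns only how the analysis is scored and named, and it says nothing about which patients should be revascularised.

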### Cost analysis

Analysis will take the form of a simple cost minimization analysis comparing a management algorithm using CTA versus ICA. Analysis will be restricted to the follow-up period within the study database and will be conducted from the health care system perspective.

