### Secondary analysis

Secondary analysis will investigate CCE and MACE, analyzed using survival analysis techniques between the ICA and CTA arms. The survival experience (that is, time-to-major adverse cardiac event) in each of the two arms will be summarized using Kaplan-Meier product limit estimates and the log-rank test will be used for comparing the survival curves. The hazard ratio with 95% confidence interval (CI) will be calculated. To adjust for possible effects of covariates on survival, the Cox’s proportional hazards model will be used. Underlying assumptions for these statistical procedures will be assessed; in particular, the proportional hazard assumption will be assessed using graphical and numerical tests, and stratified Cox models or Aalen’s additive model will be considered as needed.

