## Discussion

The proposed RCT is the largest RCT in HF patients to compare CTA versus ICA. This RCT will accomplish several goals: 1) it will determine feasibility and diagnostic accuracy of CTA in patients with undifferentiated heart failure; 2) if feasible, it will determine if the incorporation of CTA into the investigation algorithm of HF patients is cost-effective; and 3) it will determine if the CTA strategy, compared to ICA, is safe.

If these hypotheses are supported, study findings will have significant implications related to clinical practice. Evidence that CTA is effective in distinguishing etiology of HF at a lower cost with reductions in unnecessary ICA testing, subsequently with fewer procedure-associated complications, would be very attractive to clinicians and patients. This may further contribute to a reduction in healthcare costs and reduce current burdens on healthcare systems worldwide.

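### Cost minimisation is fixed without a condition that outcomes be shown equivalent, so a cost-effective conclusion with similar outcomes does not follow from the stated analyses

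*Protocol article*

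**What the plan says.** The Cost analysis section fixes the form of the economic evaluation: "Analysis will take the form of a simple cost minimization analysis comparing a management algorithm using CTA versus ICA". It restricts the analysis to study follow-up and the health-care-system perspective, and attaches no condition about outcomes.

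Equality of outcomes appears as a secondary hypothesis. Under Hypotheses, compared with ICA, "a CTA strategy will achieve: a) similar composite clinical events (CCE"; the same item covers quality of life and MACE.

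For CCE and MACE, the Secondary analysis section plans Kaplan-Meier curves and says "the log-rank test will be used for comparing the survival curves". It adds "The hazard ratio with 95% confidence interval (CI) will be calculated", with Cox models for covariate adjustment. For quality of life, the Safety section says the arms "will be compared using Student-t tests for the overall scores and utility".

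The sample size is argued from the cost regression alone, with the Design section giving "randomized to CTA versus ICA (n = 125 per group". The Abstract expects CTA to be the more cost-effective strategy with similar outcomes. The Discussion says that, if CTA proves feasible, "it will determine if the incorporation of CTA into the investigation algorithm of HF patients is cost-effective".

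**The concern.** Cost minimisation ranks strategies by cost only. The cheaper strategy is preferable if the outcomes are the same. Here sameness of outcome is something the trial sets out to examine, but the economic method is chosen as though it were settled.

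The named tests look for a difference. A large p-value from a log-rank or t-test shows only that no difference was demonstrated. The planned hazard ratio interval could address similarity, but the article gives no limit to judge it against. No analysis combining cost and effect is described, although a utility is to be compared between arms.

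At stake is the trial's headline interpretation. A lower mean cost for CTA with a non-significant clinical comparison could be reported as cost-effective when the data remain compatible with a material excess of events.

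**Working it through.** **1. The article's own power statement.** The inputs are in the Sample size and Design sections: 125 per arm, a coefficient of variation of cost of 25%, and a 10% reduction. Two-sided alpha of 0.05 is assumed, since none is stated.

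SE of the difference = 0.25 × √(2/125) = 0.0316. Power = Φ(0.10/0.0316 − 1.96) = Φ(1.20) = 88.5%.

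The claim of sufficient power is consistent with its inputs, but it concerns cost only.

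**2. Precision for clinical similarity.** The inputs are 250 patients randomised 1:1 (Design) and mean follow-up of 3 years, range 2 to 4 (Frequency and duration of follow-up). No event rate is stated. The proportion of patients with an event is therefore an assumption, varied from 10% to 50%. The upper end allows for CCE including cardiac re-hospitalisation.

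With D events and equal allocation:
- SE(log HR) = 2/√D
- 95% CI at an observed HR of 1.0 = exp(±1.96 × 2/√D)
- Power of the log-rank test at HR 1.5 = Φ(ln 1.5 / SE − 1.96)

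| Patients with event | D | SE(log HR) | 95% CI at HR 1.0 | Power for HR 1.5 | Missed |
|---|---|---|---|---|---|
| 10% | 25 | 0.400 | 0.46-2.19 | 17% | 83% |
| 20% | 50 | 0.283 | 0.57-1.74 | 30% | 70% |
| 30% | 75 | 0.231 | 0.64-1.57 | 42% | 58% |
| 50% | 125 | 0.179 | 0.70-1.42 | 62% | 38% |

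**3. Events needed to exclude an excess.** For a true HR of 1, one-sided alpha of 0.025 and 80% power, D = 4(1.96 + 0.84)²/(ln margin)². The margins are illustrations, not proposals.
- Margin 1.5: 191 events, and 191/250 = 76% of all patients.
- Margin 2.0: 66 events, and 66/250 = 26% of all patients.

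**4. Quality of life.** With 125 per arm and no losses, the 95% CI half-width is 1.96 × √(2/125) = 0.25 SD. The smallest margin with 80% power is (1.96 + 0.84) × √(2/125) = 0.35 SD. Precision is reasonable here; what is lacking is a stated criterion.

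**5. Method against conclusion.** Cost analysis yields a cost difference. The Discussion asks whether CTA is cost-effective, and the Abstract adds similar outcomes. The step between them needs either demonstrated equivalence or a joint analysis of cost and effect. The stated analyses supply neither.

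**The case against.** The strongest reply is that the primary objective, hypothesis and outcome are all average cost per patient. The regression estimate of incremental cost, with its 95% CI, is a valid cost comparison whatever label the economic analysis carries. That stands. A reader might infer that the primary result is invalid; the article does not support this.

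Other stronger readings also fail:

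- *That only difference tests are planned.* The Secondary analysis section also plans a hazard ratio with 95% CI, which is the right quantity for judging similarity. What is absent is a limit to read it against.
- *That the plan will treat non-significance as similarity.* No sentence says so. It is a risk left open by the absence of a criterion, not a stated rule.
- *That a worse strategy would look cheaper because patients who die stop accruing cost.* This is possible, but hospitalisations and further testing are costed too, so non-fatal deterioration raises cost in the worse arm. The net direction cannot be derived from the article.
- *That the Discussion promises a cost-effectiveness result.* The sentence is prefaced by a feasibility condition, and the next paragraph is conditional on the hypotheses being supported.

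A margin for a secondary outcome may also sit in a statistical analysis plan not shown here, so its absence from the article alone would be weak ground. A margin elsewhere would still not make the unconditional choice under Cost analysis match the conclusion anticipated in the Abstract and Discussion. That mismatch lies within the article.

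**Conclusion.** The point holds as a mismatch between method and conclusion and should be fixed; it is not a defect of the primary cost estimate. Cost minimisation is adopted without depending on shown equivalence, while the anticipated conclusion is cost-effectiveness with similar outcomes.

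Over an assumed 25 to 125 events, an observed hazard ratio of 1.0 would leave excesses of 119% down to 42% inside the 95% CI (upper limits 2.19 to 1.42), and a true 50% increase would be missed 83% to 38% of the time. The size depends on the event rate, which the article does not give, and on equal allocation with the usual approximation for the log hazard ratio. The finding does not turn on the rate within that range: even with half of all patients having an event, power at a margin of 1.5 is 62%. Quality of life is much less affected by sample size.

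**What to change.** 1. In Cost analysis, make cost minimisation a scenario that applies only if the confidence limits for the CCE hazard ratio and the quality-of-life difference lie inside margins set by the trial team before unblinded analysis. Otherwise report similarity as inconclusive. State that a non-significant test is not evidence of similarity.
2. Add a joint cost-and-effect analysis: QALYs from the utility named in the Safety section, with utility 0 from death, incremental net benefit, and a bootstrap that resamples each patient's cost and QALY together. This depends on the utility measurement schedule, which the article does not show, so first confirm that it permits QALYs.
3. If step 2 is not done, limit the conclusion in the Abstract and Discussion to a difference in cost and remove the term cost-effective.

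The cost is wording plus extra analysis of data already planned, with no additional patients. The drawback is that the similarity statement will often be inconclusive: a margin of 1.5 needs 191 events for 80% power, which 250 patients are unlikely to supply. The primary cost analysis is unchanged.
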